##### Physical exercise protocol (Functional Capacity)

To determine the pregnancy-specific anaerobic threshold (AT), all women will perform an incremental exercise sub-maxim test of the ramp type on a mechanically braked cycloergonometer (Monarck 820K.) at a bench height to facilitate the most effective pedalling. Participants will be instructed to perform the test for as long as possible to ensure a true maximal attempt. Standard ACSM test termination criteria will be monitored and followed throughout each test. After a 3-minute warm-up at 20 W, the work rate will increase every minute by 15 wattios (W). Throughout the test the pedalling rate will be set up at 60 rpm. The pregnant women will be monitored by blood pressure and heart rate, and will be required to estimate their level of exhaustion every minute on Borg's Ratio of Perceived Exertion scale. The incremental workload will be discontinued when one of the following criteria will be met: heart rate of 160 beat per minute, or the maximum level of exhaustion on Borg's scale; another 3-minute workload will be realized at 10 W followed for cooling down before completion of the exercise test.

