### Specific objectives

1. To determine the influence of aerobic exercise on the functional capacity (VO_2Max_), anthropometry (Fatness, body mass index [BMI]) and biochemical markers (glucose and lipid profile) in the target population.

2. To study the influence of controlled exercise on endothelial function of pregnant women.

3. To evaluate the effect of aerobic exercise on biochemical markers of insulin resistance (HOMA Index).

4. To evaluate the effect of physical exercise on maternal variables (route of delivery, duration of childbirth, postpartum complications) and the newborn (APGAR score and anthropometry).

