### Outcome measurements and instruments

The primary outcome is the difference on endothelium-dependent brachial artery flow-mediated dilatation after three months of regular aerobic exercise. [Time Frame: Baseline and 32 weeks gestation]

The secondary outcome measures are High Sensitivity C-Reactive Protein, Nitrates, Nitrites, cyclic cyclic guanosine monophosphate (cGMP), blood lipid profile and glucose, HOMA index, anthropometric indicators, functional capacity (VO_2Max_), [Time Frame: Baseline and 32 weeks gestation] and maternal pregnancy outcomes (type delivery, duration of childbirth, blood pressure evolution, postpartum complications) and newborn outcomes (APGAR score and anthropometry), [Time Frame: Delivery].

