### Interventions

#### Exercise Group

Regular aerobic physical exercise: Walking (10 minutes), aerobic exercise (30 minutes), stretching (10 minutes) and relaxation exercise (10 minutes) for 3 months. Exercise will be performed during 3 sessions per week. All sessions will be supervised by a physical therapist and a physical educator. The exercise-program follows the American College of obstetricians and gynecologist (ACOG) [27] and the American college of Sports Medicine (ACSM] exercise prescription [28]. Aerobic activities will be performed at moderate intensity (60-70% of maximal heart rate) measured by the 6-20 Borg's rating scale (PER). Each session will start with a 5 minutes warm up, followed by 30 minutes of aerobic activity, including a 5 minutes cool down. This is followed by 15 minutes of exercises circuit strength training of the upper limbs, lower limbs, and deep abdominal muscles stabilization. The last 5 minutesconsist of stretching and relaxation exercises.

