#### Eligibility

64 pregnant nulliparous women, healthy, 16 to 30 years old. *Appendix 2*.

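### A sub-maximal test capped at 160 beats per minute cannot ensure a true maximal attempt, so VO2max in women stopped by the cap is an estimate and should be named as one (minor)

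*Protocol article*

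**What the plan says.** Three statements in the Protocol article, *Physical exercise protocol (Functional Capacity)*, bear on how hard the women work:

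- Type and purpose of the test: "To determine the pregnancy-specific anaerobic threshold (AT), all women will perform an incremental exercise sub-maxim test of the ramp type".
- Effort: "Participants will be instructed to perform the test for as long as possible to ensure a true maximal attempt".
- End of the increments, on whichever comes first: "heart rate of 160 beat per minute, or the maximum level of exhaustion on Borg's scale". The section adds that the standard ACSM termination criteria are followed throughout.

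The result is named functional capacity with VO2max in brackets. That label appears in *Specific objectives* (objective 1), in *Outcome measurements and instruments* (a secondary outcome at baseline and 32 weeks), and in *Baseline assessments and active follow-up* (Visit B, repeated at Visit C). None of these places calls it an estimate.

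*Eligibility* gives the population: "64 pregnant nulliparous women, healthy, 16 to 30 years old". *Statistical Analysis* compares the groups after treatment with a t test, or with a Mann-Whitney test where the distribution is not normal.

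**The concern.** One section gives the test two incompatible properties: it is sub-maximal with a heart-rate ceiling, and it ensures maximal effort. The outcome label follows the second property, while the stopping rule follows the first. At stake is what the reported number means. A reader who sees VO2max in the results may take it for a measured maximum, although for some women it would be inferred from work below their maximum. This concerns the definition of one secondary outcome.

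**Working it through.** The article states no figure for this point, so there is none to reproduce. The check compares the statements and then gauges how far below maximum the cap lies.

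**Step 1: the two stopping routes**

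| Reason the increments stop | Maximal attempt? | Status of VO2max |
|---|---|---|
| Maximum Borg exhaustion, below 160 beats per minute | Possibly, as the woman perceives it | Could reflect a maximum |
| 160 beats per minute, before maximum Borg | No | Can only be an estimate |

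The word *ensure* fails on the second route. The article does not say how many women would stop that way. The conclusion for that route does not depend on how oxygen uptake is obtained: even with gas analysis, uptake at the cap is not the maximum.

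**Step 2: where the cap lies**

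Inputs: the cap of 160 (*Physical exercise protocol*) and ages 16 to 30 (*Eligibility*). Maximal heart rate (HRmax) is not given, so it is assumed: two age formulas, and a wider plain range of 170 to 204.

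Formulas: share of maximum = 160 / HRmax; shortfall = HRmax − 160.

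| Assumed HRmax | Basis | 160 / HRmax | Shortfall (beats/min) |
|---|---|---|---|
| 204 | 220 − 16 | 78.4% | 44 |
| 196.8 | 208 − 0.7 × 16 | 81.3% | 36.8 |
| 190 | 220 − 30 | 84.2% | 30 |
| 187 | 208 − 0.7 × 30 | 85.6% | 27 |
| 180 | plain range | 88.9% | 20 |
| 170 | plain range, low end | 94.1% | 10 |

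The cap is below maximum in every row. It would cease to be so only for a woman whose maximum is 160 or less.

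**Step 3: the separate improvement**

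VO2max is collected at both Visit B and Visit C, but the stated comparison uses only the later value. Adjusting for the Visit B value by analysis of covariance (ANCOVA) multiplies the variance of the group difference by about 1 − r², where r is the correlation between the two visits. The article gives no r, so a range is assumed:

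- r = 0.3: 1 − 0.09 = 0.91, a reduction of 9%
- r = 0.5: 1 − 0.25 = 0.75, a reduction of 25%
- r = 0.8: 1 − 0.64 = 0.36, a reduction of 64%

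**The case against.** The strongest reply is that this is one loose sentence. The operative rule is clear: the ACSM criteria apply throughout, and the increments end at 160 beats per minute or maximum Borg. The wish for a maximal attempt is addressed to the participants and is bounded by those stops. The section also tells the reader that the test is sub-maximal. This largely stands, and it is why the point is minor. It does not rescue the claim to ensure a maximal attempt or the unqualified label in the objectives, outcomes and visit schedule. The article does mark other derived quantities: LDL-C is described as estimated by a named formula, and body composition as obtained by indirect formulas.

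A reader might infer four stronger things, none of which the document supports.

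- **That staff are told to push pregnant women past the safety limit.** The stops govern, and nothing permits continuing the increments beyond them.
- **That the missing VO2max equation, or the absence of any mention of gas analysis, is an error.** A condensed article may leave such detail out. This one refers to an operations manual and to a fuller published description.
- **That the choice of heart-rate formula harms the comparison.** It would change absolute values according to age, but it acts alike on both randomised arms and creates no systematic difference between them.
- **That unblinded women in one arm may persist longer and bias the result.** This requires the result to depend on the final stage reached, which the article does not say. Deleting the sentence would not remove the route either, because the Borg stop stays.

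It can also be said that the same exhortation in both arms standardises effort. The common stopping criteria already set the same rule for ending the test in both arms.

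**Conclusion.** The point holds as an inconsistency of wording and labelling. The capped test cannot ensure a maximal attempt, and VO2max is necessarily an estimate in women stopped at 160 beats per minute. The cap lies at 78% to 94% of maximum if maximal heart rate is 204 down to 170, an assumed range. The share of women affected is unknown. Severity is minor: the primary FMD outcome and the sample size are unaffected, the stops are clear, and no bias between arms is shown.

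The unadjusted week-32 comparison is a separate matter. Under randomisation it is valid, but it leaves a baseline value that is already collected unused. The gain from adjustment depends entirely on r, which is not given.

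**What to change.** 1. In *Physical exercise protocol (Functional Capacity)*, delete the sentence about a true maximal attempt. Keep the 160 beats per minute, Borg and ACSM stops unchanged.
2. In *Specific objectives*, *Outcome measurements and instruments* and *Baseline assessments and active follow-up*, name the outcome *estimated VO2max*, derived the same way at Visits B and C.
3. Separately, in *Statistical Analysis*, compare the groups at week 32 by ANCOVA with the Visit B value as covariate, in place of the after-treatment-only t test.

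The first two changes cost one deleted sentence and one added word in three places, plus a statement that the derivation is the same at both visits. The third uses data already scheduled. No visit, device, participant or safety rule changes. The sentence on the anaerobic threshold can stay, since a test may serve more than one purpose.

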##### Measurement of flow-mediated dilatation of the brachial artery

Endothelium-dependent vasodilatation will be measured using the technique introduced by Celermajer et al. [23], using the guidelines reported by Corretti et al. [34]. The diameter of the brachial artery will be assessed using a high-resolution ultrasound device (Siemens SG-60, USA), equipped with a 7.5 MHz linear array transducer and an integrated electrocardiography package. The ultrasound procedures will be performed with the subject resting quietly in supine position for at least 10 minutesAll measurements will be taken at end-diastole triggered by electrocardiogram. First, the diameter of the right brachial artery will be searched in a cross-sectional view and then scanned over a longitudinal section 5 to 10 cm proximal to the right elbow. The diameter of the brachial artery will be measured from the anterior to the posterior intima/lumen interface at a fixed distance. The mean diameter will be calculated from 4 cardiac cycles. After that, a pneumatic tourniquet placed around the right forearm will be rapidly inflated to at least 50 mm Hg above the systolic blood pressure for 5 minutesA sudden release of the cuff will induce an increase in blood flow in the brachial artery located proximal to the tourniquet. During reactive hyperemia, there will be an increase in shear stress, causing endothelium-dependent vasodilatation, mainly due to endothelial release of nitric oxide [35]. This secondary dilation enhances and prolongs the reactive hyperaemic phase. FMD of the brachial artery will be measured 45-60 s after cuff release. The change in diameter caused by the increased flow will be calculated as the percentage change relative to the baseline measurement (FMD%). The dilator brachial artery response due to shear stress has been shown to have a good accuracy and reproducibility [24,36,37]. Images will be recorded on DVD player, and the measurements will be done by two observers blinded to the study and then both measurements will be averaged.

##### Biochemical markers

The routine clinical test and those of the endothelial function and inflammation markers will be processed in the Proteins, Enzymes and Biochemistry Laboratory, from the Universidad of Valle (Cali, Colombia).

**Plasma glucose levels**: Glucose levels will be measured by enzyme assay kits, using the A-15 analyser (Biosystems, España).

**Insulin**: Insulin will be determined by chemiluminescent immunometric assay (IMMULITE^® ^Automated Analyzer, Diagnostic Products Corporation, Los Angeles, USA).

**Lipid profile**: Total cholesterol, triglycerides and HDL cholesterol (HDL-C) levels will be measured by enzyme assay kits, using the A-15 analyser (Biosystems, Spain). Estimates of LDL-C concentration will be calculated using the Friedewald formula [38].

**High-sensitivity C - reactive protein (CRP): **the fasting plasma CRP concentrations will be analyzed by high sensitivity turbid meter technique using the use automatic analyzer and reagents (Biosystems, Spain) [39].

**Biomarkers of the endothelial function. Measurement of the NO in serum**: NO is rapidly converted to nitrate and nitrite. The measurement of these metabolites are used to estimate NO production The NOx (nitrate plus nitrite), concentrations in serum will be determined using a commercial kit (Nitrate/Nitrite Colorimetric Assay Kit, Cayman Chemical, USA). The within-day and between-day coefficients of variation for this assay are less than 5% at a concentration of 50 μmol/l [40]. Subjects will receive a standardized low-nitrate diet for 24 hours before testing to avoid the effect of nitrates in the diet.

**Measurement of the cGMP Level in Plasma: **blood will be collected in citrate anticoagulated tubes and immediately centrifuged. Plasma will be deproteinized by addition of 25 volumes of absolute ethanol and boiled before centrifugation. After evaporation, the sample will be dissolved in 0.05 mol/L Na-acetate buffer, pH 6.2. cGMP will be acetylated to be measured by radioimmunoassay after succinylation (Kit Colorimetric Assay. Cayman Chemical, USA) [41].

#### Nutrition

The pregnant women will answer three nutritional questions: 1) Did the participant eat meat the week before and if so, how much, 2) Did the participant eat fried food the week before and if so how often, and 3) How often did the participant eat vegetables the previous week [42].

#### Statistical Analysis

There will be an exploratory analysis which will include mean values and standard deviations of each of the variables studied to determine the balance at baseline between the groups. Normality of distribution will be checked for all variables using the Kolmogorov-Smirnov test.

The primary outcome will be the differences on endothelium-dependent brachial artery flow-mediated dilatation between the groups; and the secondary outcomes will be the differences related to anthropometric, functional and metabolic parameters, and pregnancy outcomes. The comparison between the groups will be made after treatment using the student t test for those variables with normal distribution and the non parametric Mann-Whitney test for those with non-normal distribution. Then, a linear regression analysis will be performed to determine the effect for each variable on the FMD, modeling it with Greenland parameters to determine which variable has a relationship with the model. Statistical analyses will be carried out using the SPSS software (version 14.0, SPSS, Chicago, IL). A p value < 0.05 will be considered statistically significant.

#### Study conduct and monitoring

The study will be conducted according to Good Clinical Practice and standard operating procedures. It will be monitored by the Human Rights Committee at the Universidad del Valle Coordinating Center composed of experts in physical exercise, physicians, gynecologists, nurses, physical therapists, physical educators, clinical epidemiologists and bacteriologists. Interim monitoring reports will be submitted to the experts, focusing on patient intake, adherence to protocol, baseline comparability of treatment groups, completeness of data retrieval, and adverse events. All adverse events will also be reported to the Universidad del Valle Ethics Committee. To standardize study procedures, an operations manual has been written and comprehensive training sessions will be held prior to the initiation of the trial. In addition, there will be weekly conference calls between the sites, the Coordinating Center, and the research chief to review procedures and address problems. To ensure the uniformity and quality of the interventions at each site, experts in exercise physiology will train all the therapists prior to the trial initiation and consult with them on an ongoing basis. The Coordinating Center has initiated procedures to ensure the quality and integrity of the data. These include inspections of the data forms as they are received from sites and periodic reviews of the computer data files to identify out of range values and missing data forms.

#### Ethical aspects

The clinical trial will be conducted according to the Helsinki's Declaration, the Good Clinical Practice Guidelines and the Colombian legislation (Resolution 8430/93 of the Ministry of Health). The patient will provide written informed consent in a form designed for such purpose. The information generated by the study will be confidential and strictly limited to the purposes stipulated in the protocol. The patient may refuse to continue participating in the study at any moment after providing consent. The study has been approved by both Universidad del Valle Ethics committee and that of Fundación Cardiovascular de Colombia. All assessments will be performed by trained staff. The blood samples will be collected in aseptic conditions by an expert bacteriologist. A complete description of the design and methods of this RCT, which was in accordance with CONSORT guidelines http://www.consort-statement.org was recently published [43].

#### Study timeline

The study will last 36 months. Figure 3.

**Figure 3 F3:**
[figure not shown]
**Study Timeline**. CRF: Case report format.

## Abbreviations

PE: Preeclampsia; LBW: Low Birth Weight; IUGR: Intrauterine Growth Restriction; NO: Nitric Oxide; PGI_2_: Prostacyclin; TXA_2_: Thromboxane A_2_; FMD: Flow Mediated Dilatation; CRP: C-Reactive Protein; O_2_^-^: Superoxide; BMI: Body Mass Index; cGMP: cyclic guanosine monophosphate; ACOG: American College of obstetricians and gynaecologist; ACSM: American college of Sports Medicine; PER: Borg's rating scale; hs-CRP: High sensitivity C - reactive protein; SBP: Systolic blood pressure; DBP: Diastolic blood pressure; MBP: Mean blood pressure; W: Wattios; HDL-C: High density lipoprotein cholesterol; LDL-C: Low density lipoprotein cholesterol; NOx: Nitrate plus nitrite; CRF: Case report format.

## Appendices

### Appendix 1. Content of the sessions of Prenatal Behavioural Control

Session 1

Introduction

• Overview of treatment

• Instructions on how to keep activity diary; how to select activities based on PER.

Session 2

• Watch videotape on stretching and review stretching

• Supervised stretching

• Check activity diary

Session 3

• Instruct pregnant women about ways to incorporate activities into lifestyle

• Check activity diary

Session 4

• Watch videotape on relaxation exercises

• Supervised exercises

• Check activity diary

Session 5

• Instructions on maternal nutrition

• Check alimentation diary

Session 6

• Instructions on intrauterine stimulation

• Supervised activity

• Check activity diary

### Appendix 2. Selection criteria

Inclusion Criteria:

▪ Nulliparous women who have not participated in a structured exercise program during pregnancy.

▪ Living fetus at the routine ultrasound scan and a normal pregnancy.

▪ Gestational age 16 to 20 weeks.

▪ Written informed consent will be obtained from each woman prior to the inclusion in the study.

Exclusion Criteria:

▪ History of high blood pressure.

▪ Chronic medical illnesses (cancer, renal, endocrinologic, psychiatric, neurologic, infectious and cardiovascular diseases).

▪ Persistent bleeding after week 12 of gestation.

▪ Poorly controlled thyroid disease.

▪ Placenta praevia, incompetent cervix, polyhydramnios, oligohydramnios.

▪ History of miscarriage in the last twelve months.

▪ Diseases that could interfere with participation (following recommendations from ACSM 2000, ACOG 2002).
